## Abstract

**Background:**

The current management guidelines recommend that patients with borderline resectable pancreatic adenocarcinoma (BRPC) should initially receive neoadjuvant chemotherapy. The addition of advanced radiation therapy modalities, including stereotactic body radiation therapy (SBRT) and intraoperative radiation therapy (IORT), could result in a more effective neoadjuvant strategy, with higher rates of margin-free resections and improved survival outcomes.

**Methods/design:**

In this single-center, single-arm, intention-to-treat, phase II trial newly diagnosed BRPC will receive a “total neoadjuvant” therapy with FOLFIRINOX (5-fluorouracil, irinotecan and oxaliplatin) and hypofractionated SBRT (5 fractions, total dose of 30 Gy with simultaneous integrated boost of 50 Gy on tumor-vessel interface). Following surgical exploration or resection, IORT will be also delivered (10 Gy). The primary endpoint is 3-year survival. Secondary endpoints include completion of neoadjuvant treatment, resection rate, acute and late toxicities, and progression-free survival. In the subset of patients undergoing resection, per-protocol analysis of disease-free and disease-specific survival will be performed. The estimated sample size is 100 patients over a 36-month period. The trial is currently recruiting.

**Trial registration:**

NCT04090463 at clinicaltrials.gov.

## Background

The term “borderline resectable” pancreatic cancer (BRPC) indicates a disease with major venous involvement (solid tumor contact greater than 180 degrees with superior mesenteric vein/portal vein, or contour irregularity of the vein, or thrombosis) and/or arterial abutment (solid tumor contact of less than 180 degrees with superior mesenteric artery and/or celiac trunk) upon thin-slice cross-sectional imaging [1]. The National Comprehensive Cancer Network® guidelines recommend that borderline resectable patients receive primary chemotherapy or chemoradiation, because upfront resection would likely be compromised by positive surgical margins [1]. Although there is no robust evidence to recommend specific chemotherapy regimens off-experimental protocols, the most commonly used regimens include FOLFIRINOX (5-fluorouracil, irinotecan and oxaliplatin) and gemcitabine plus nanoalbumin-bound (nab)-paclitaxel, that have been recently empirically translated from randomized trials of metastatic disease to earlier stages, given the higher response rate relative to gemcitabine alone [2, 3]. In a large observational study of primary chemotherapy for newly diagnosed patients with localized disease, the resection rate in the subgroup of BRPC approached 25%, with the highest rate being reached in patients < 75 years who received FOLFIRINOX (51%). Following resection, the median overall survival was 35.4 months. Cohort-based independent prognostic factors were completion of at least 6 months of chemotherapy, complementary radiation therapy, and resection [4]. This constituted the backbone reference for integrating chemotherapy and radiation therapy into a “total neoadjuvant” approach.

Although in the recent PREOPANC-1 trial preoperative chemoradiotherapy did not show a significant overall survival benefit relative to a surgery-first approach, the outcomes of the secondary end points and predefined subgroup analyses suggest an advantage of the neoadjuvant approach [5]. Remarkably, patients in the experimental arm were treated with an outdated chemotherapy regimen (gemcitabine) and moderately fractionated external-beam radiation (36 Gy administered in 15 fractions). In another single-arm, phase 2 clinical trial conducted at the Massachusetts General Hospital from 2012 to 2016, 48 patients with BRPC received FOLFIRINOX for 8 cycles. Upon restaging, patients with resolution of vascular involvement received short course chemoradiotherapy (5 Gy × 5 with protons) with capecitabine. Patients with persistent vascular involvement received long course chemoradiotherapy with fluorouracil or capecitabine. A margin-negative resection (primary endpoint) was achieved in 65% (intention-to-treat) and 97% of patients (per-protocol). The median progression-free survival (PFS) and OS among all eligible patients were 14.7 and 37.7 months. In patients who underwent resection, the median PFS was 48.6 months, and the median OS was not reached at a median follow-up of 18 months [6]. These latter results confirmed that a total neoadjuvant approach with multiagent chemotherapy and individualized radiation resulted in a high rate of R0 resections and prolonged median PFS and OS.

Advanced radiation therapy techniques, including Stereotactic Body Radiation Therapy (SBRT), have emerged as an attractive solution for BRPC, enabling the delivery of large doses of radiations in fewer fractions relative to the conventional, long-course radiation therapy. In this regard, it has been suggested that preoperative SBRT following up to 6 months of primary chemotherapy might further improve the likelihood of a margin-negative resection and OS over chemotherapy and conventional chemoradiation [7]. At present, the optimal SBRT schedule for BRPC has yet to be determined, with only a few published studies reporting remarkable differences in dose and fractionation [8–11]. Mellon et al. treated 110 BRPC patients with SBRT delivered in 5 consecutive daily fractions with a median total dose of 30 Gy to the tumor and a 40 Gy dose painted to the tumor-vessel interface (TVI) [8]. The R0 resection rate was 96%, and the median OS for resected patients 34.2 months. A recent phase I trial investigated a total neoadjuvant approach with FOLFIRINOX followed by dose escalated SBRT [11]. The maximum tolerated dose of SBRT was 36 Gy in 3 fractions to the tumor, with a boost to the posterior margin (defined as the area between the posterior 1 cm of the tumor and mesenteric vessel/retroperitoneal soft tissue) up to 45 Gy in 3 fractions. The R0 resection rate was 66.6%, the median OS for resected patients was not reached, and no grade ≥ 3 adverse events were reported. In a recent observational study from the authors’ Institution, 88.9% of BRPC patients received surgical resection following multiagent chemotherapy and SBRT with simultaneous integrated boost (SIB) and simultaneous integrated protection (SIP) [12]. The prescribed dose was 50/30/25 Gy in 5 consecutive daily fractions to TVI (SIB)/planning target volume (PTV) tumor/overlap area between PTV and organs at risk (SIP), respectively. No acute or late grade ≥ 3 SBRT-related adverse events were observed. However, about 40% of patients experienced an R1 resection. In more than 70% of R1 patients, microscopic residual occurred at the posterior margin/retroperitoneal lamina, and the performed dosimetric evaluation showed a predominant incidence of in-field recurrence, with a recurrence median dose of 40.42 Gy. In this respect, current recommendations support the application of intraoperative radiation therapy (IORT) as a boost strategy (integrated for a dose-escalation multimodality approach) to maximize local control and impact upon survival [13].

IORT is the application of a single fraction of radiation therapy to the target volume at the time of surgery while sparing the surrounding organs. Data regarding IORT in PC have been evaluated in retrospective single- or multi-institutional series, showing 40–80% reduction of loco-regional recurrence as compared to the standard treatment [14]. When applied to PC, IORT was associated to consistent benefits in terms of overall survival, either in the surgery plus IORT group, and in the locally advanced PC group, where IORT was the only local treatment [15–18].

In the light of the most recent results of multiagent chemotherapy regimens and radiation therapy techniques, we herein propose a phase II trial of total neoadjuvant treatment with FOLFIRINOX, hypofractionated SBRT with SIB/SIP, and IORT (following the resection phase, or as an in situ treatment) in newly diagnosed BRPC.

## Methods/design

The study reporting adheres to the SPIRIT Guidelines [19]. This single-arm phase II trial will be conducted at the University of Verona Hospital Trust and will enroll newly diagnosed patients with BRPC. The trial has been registered at www.clinicaltrials.gov (NCT04090463) and has been approved by the local Ethics Committee (#2301CESC). The expected total study duration is 72 months (36 months for enrollment and 36 months for follow-up).

### Endpoints

The primary endpoint is the 3-year disease-specific survival (intention-to-treat). Secondary endpoints include:
Completion of chemotherapy,Completion of SBRT,Acute and late toxicities,Resection rate,Perioperative morbidity and mortality,Rate of margin-free surgery,Progression-free survival (local/distant progression), intention-to-treat,Recurrence-free survival in the subset of patients undergoing resection (per-protocol),3-year disease-specific survival in the subset of patients undergoing resection (per-protocol).

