### Statistical considerations

#### Sample size calculation

The estimate of accrual was calculated hypothesizing that total neoadjuvant therapy with FOLFIRINOX + SBRT + IORT will improve the 3-year survival rate up to 37% in comparison with cohort-level institutional data (patients < 75 years with BRPC undergoing neoadjuvant FOLFIRINOX, 3-year survival of 23.7%) Accrual time was set at 36 months and follow-up at 36 months. At a power of 0.90, and alpha of 0.5 a sample size of 100 patients was calculated assuming a non-parametric estimate of survival distribution. The SWOG Cancer Research and Biostatistics one-arm trial with time-to-event data sample size calculator was employed [26].

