#### Survival analysis

The progression-free survival (for patients who will not ultimately receive pancreatectomy due to unexpected locally unresectable or metastatic disease) and the disease-specific survival (for patients receiving pancreatectomy) will be calculated from both the date of diagnosis and the date of last follow-up or recurrence/death from disease, using the Kaplan-Meier method. Pairwise differences in survival will be assessed using the log-rank test. The analysis of recurrence and survival predictors will be carried out using the proportional hazard Cox regression (backward stepwise elimination technique, Wald method, *P* < .05 for entry, *P* > .10 for removal). Statistical significance will be determined by a 2-sided *P* value less than .05. Data will be using SPSS software (IBM).

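### The primary endpoint is disease-specific survival under Endpoints but unqualified survival in the abstract and the sizing; if the 23.7% benchmark is all-cause, the comparison favours success

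*Protocol article*

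**What the plan says.** - **Endpoints:** "The primary endpoint is the 3-year disease-specific survival (intention-to-treat". The resected subset has its own disease-specific survival endpoint, listed as secondary.
- **Abstract, Methods/design:** "The primary endpoint is 3-year survival". The same paragraph uses the term disease-specific only for the resected subset.
- **Sample size calculation:** the strategy "will improve the 3-year survival rate up to 37% in comparison with cohort-level institutional data". The comparator is patients under 75 with "BRPC undergoing neoadjuvant FOLFIRINOX, 3-year survival of 23.7" percent. Neither rate is labelled overall, all-cause or disease-specific.
- **Survival analysis:** time runs to last follow-up or "recurrence/death from disease, using the Kaplan-Meier method". Disease-specific survival is mentioned here only for patients who have a pancreatectomy.

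The article does not define a disease-specific death or say how toxic or perioperative deaths are classed. It does plan to record 90-day postoperative mortality, and it requires grade 5 events to be reported whatever their attribution.

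**The concern.** All-cause and disease-specific survival are different endpoints, and disease-specific survival can never be the lower of the two. A single-arm trial succeeds or fails against a fixed external rate, so the endpoint and that rate must count the same deaths. If the trial leaves out some deaths that the benchmark includes, it can pass without any gain in survival.

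The deaths most likely to be left out are those caused by chemotherapy, radiotherapy or surgery, which are a cost of the strategy under test. Assigning a cause of death also calls for judgement, and there is no control arm in which the same judgement would be applied. With two labels in print, the choice between them could be made after the data are seen.

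**Working it through.** **1. Does the sizing rest on the rates labelled survival?**

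The inputs from Sample size calculation are p0 = 0.237, p1 = 0.37, power 0.90 and N = 100: "At a power of 0.90, and alpha of 0.5 a sample size of 100 patients was calculated". Also "Accrual time was set at 36 months and follow-up at 36 months", so every patient can be observed for 36 months and the non-parametric variance is essentially binomial. Alpha is taken as 0.05 one-sided (z = 1.645, with 1.282 for power).

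- Arcsine: n = [(1.645 + 1.282) / (2(asin√0.37 − asin√0.237))]² = (2.926 / 0.2909)² = 101.2.
- Plain proportion: n = [(1.645·√(0.237·0.763) + 1.282·√(0.37·0.63)) / 0.133]² = (1.318 / 0.133)² = 98.2.

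The stated 100 is reproduced, so the figure labelled survival is the bar for success. The printed alpha of 0.5 gives only 14-22 patients one-sided and 33-50 two-sided. Two-sided 0.05 gives 119-124 with the plain, arcsine and complementary log-log forms, although Survival analysis says "Statistical significance will be determined by a 2-sided". That is a separate defect.

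**2. What would disease-specific survival read if nothing improved?**

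The assumptions, none of them in the article, are that 23.7% is all-cause, that true all-cause survival in the trial is also 23.7%, and that non-disease deaths are censored.

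*Case A.* A share f of deaths is not from disease, with proportional hazards, so the Kaplan-Meier estimate tends to 0.237^(1−f). *Case B.* A fraction m of all patients dies early of treatment and is censored, so the estimate tends to 0.237/(1−m).

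The arcsine approximation to false success is Φ[2√100·(asin√p − asin√0.237) − 1.645], where p is the value read.

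| Assumed | Reads | False success, arcsine approximation |
|---|---|---|
| A, f = 3% | 24.8% | 0.08 |
| A, f = 5% | 25.5% | 0.11 |
| A, f = 10% | 27.4% | 0.21 |
| B, m = 2% | 24.2% | 0.06 |
| B, m = 5% | 24.9% | 0.09 |
| B, m = 10% | 26.3% | 0.15 |

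**3. Does the choice of test matter?**

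The article does not name the primary test. Simulation of 20,000 trials of 100 patients compared two versions:

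- Null standard error, √(0.237·0.763/100) = 0.0425: 0.09, 0.13 and 0.24 for case A, and 0.07, 0.10 and 0.17 for case B. This version already rejects in about 0.06 of trials with no bias.
- Greenwood standard error: 0.07, 0.09 and 0.18 for case A, and 0.05, 0.07 and 0.12 for case B. This version starts at about 0.04.

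The quoted ranges, 8-24% and 6-17%, run from the arcsine figure at the smallest assumed share to the null-standard-error figure at the largest. A Greenwood test sits somewhat lower. Under every version the rate rises with the share of censored deaths.

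**4. What if the benchmark is disease-specific?**

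Numerator and bar then count the same deaths, and the mismatch bias is zero.

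**5. What if disease-specific survival is kept and the bar is raised to match?**

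With 23.7% all-cause and case A, the bar becomes 24.8%, 25.5% or 27.4%. Against 37% (arcsine, one-sided 0.05, power 0.90), N is about 121, 138 or 201. Power with 100 patients is 0.85, 0.80 or 0.66.

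**The case against.** A reader might infer that the comparison is biased as a matter of fact. The article does not support that. It never calls the 23.7% all-cause, and the institutional data behind it are not shown. The abstract uses the bare word survival for the endpoint that the Endpoints section makes disease-specific, so the authors may use the word loosely and the benchmark may itself be disease-specific. Against this, the abstract uses disease-specific as a distinct term for the resected subset in the same paragraph, which makes all-cause the plainer reading of the bare word. It remains a reading.

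A reader might also infer a rule that treatment-related deaths are censored. No such rule is stated. It is the natural sense of counting deaths from disease under Kaplan-Meier, but some definitions class treatment deaths as events, and the full protocol may contain one. The Survival analysis sentence ties disease-specific survival to resected patients, so it is not a clean event rule for the intention-to-treat endpoint. It is weaker still as evidence on progression-free or recurrence-free survival, and nothing here relies on it for those.

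Nor would toxic deaths go unseen. Toxicity and perioperative mortality are secondary endpoints, and grade 5 events are reported regardless of attribution. What stands is that such deaths may fall outside the primary test.

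Larger non-disease shares give more dramatic error rates, but nothing in the article points to them. Treatment deaths also tend to come early, where the effect is smaller. Finally, disease-specific survival against a matched benchmark would be coherent, so all-cause survival is a preference and not the only remedy.

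**Conclusion.** The contradiction is established from the text: the primary endpoint is disease-specific in the Endpoints section and unqualified survival in the abstract and the sizing. It concerns what the trial will claim, so it is not a detail to leave to an analysis plan.

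The bias is conditional. It needs an all-cause benchmark and censoring of non-disease deaths, both natural readings and neither stated. Under the assumed shares a nominal 5% one-sided error becomes about 8-24% (3-10% of deaths not from disease) or about 6-17% (2-10% of patients dying early of treatment). Without the first condition the mismatch bias is zero. If treatment-related deaths count as events, it shrinks to whatever other non-disease deaths contribute.

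**What to change.** Use one primary endpoint, with one event definition, in the abstract, Endpoints, Sample size calculation and Survival analysis, and state what the 23.7% counts.

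**Preferred:** 3-year all-cause survival in all enrolled patients. This matches the abstract and the sizing as they read and leaves N at about 100 if 23.7% is all-cause. If it is not, use the cohort's all-cause figure and recompute. Keep disease-specific mortality as a secondary endpoint, estimated by cumulative incidence with other deaths as competing events.

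**Alternative:** keep disease-specific survival as primary, with a disease-specific benchmark from the same cohort, a statement that treatment-related deaths count as events, and restated power. If the matched bar is higher than 23.7% and 37% remains the target, 100 patients give less than 0.90 power, as shown above.

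**Cost:** under the preferred route, a wording amendment and a slightly less favourable point estimate. Grade 5 events are already reported regardless of attribution, and follow-up already runs to death or study completion, so little or no new data collection should be needed.

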### Study population

#### Inclusion criteria

Biopsy-proven, previously untreated BRPC, defined according to the NCCN guidelines v3.2019 [1],Age 18–75 years,Eastern Cooperative Oncology Group (ECOG) performance status 0 or 1,Adequate bone marrow function (absolute neutrophil count ≥1500 per cubic millimeter; platelet count ≥100.000 per cubic millimeter; hemoglobin level ≥ 10 g per deciliter), liver function (serum total bilirubin level ≤ 1.5 times the upper limit of the normal range), and renal function (creatinine clearance ≥50 ml per minute),Ability to understand the characteristics of the clinical trial,Written informed consent.

#### Exclusion criteria

Ampullary, biliary, or duodenal adenocarcinoma; pancreatic adenocarcinoma in the background of an intraductal papillary mucinous neoplasia (IPMN), other uncommon pancreatic adenocarcinomas (acinar-cell, squamous, giant-cell osteoclastic-like),Primary tumor > 60 mm,Invasive cancer in the last 5 years requiring radiation therapy to the upper abdomen or chemotherapy,Symptomatic heart failure or coronary artery disease,Pregnant or lactating women,Impaired mental state or language problems.

### Procedures

#### Diagnostic assessment and treatment allocation

PC is diagnosed using thin-slice cross-sectional imaging (contrast-enhanced tri-phasic computed tomography of the thorax and abdomen) or gadolinium-enhanced magnetic resonance. 18-FDG positron-emission tomography is performed to rule out suspected distant metastases (indeterminate liver/pulmonary lesions on cross-sectional imaging). Tissue diagnosis is performed via endoscopic ultrasound or transabdominal ultrasound guided fine-needle aspiration. Baseline serum carcinoembryonic antigen (Ca) 19.9 is measured at the time of diagnosis, per standard practice. In jaundiced patients, endoscopic retrograde cholangiopancreatography (ERCP) is performed, and self-expandable fully covered metal biliary stent is placed. Ca 19.9 assessment is repeated following biliary drainage (ideally when bilirubin drops to < 3 mg/dL). All newly diagnosed patients with BRPC will be collegially evaluated in a multidisciplinary meeting (The Verona Pancreas Institute Oncologic meeting) and screened for inclusion by dedicated Oncologists, Radiation Oncologists, and Surgeons.

#### Chemotherapy

Following informed consent, FOLFIRINOX will be administered either in Verona or in local hospital operating within a regional oncologic network on a 14-day cycle for up to 12 cycles (minimum 8). Fluorouracil will be administered as a 400-mg/m2 bolus on day 1, then as a 2400 mg/m2 continuous infusion for 46 h. Leucovorin calcium, 400 mg/m2; oxaliplatin, 85 mg/m2; and irinotecan hydrochloride, 180 mg/m2, will be administered on day 1. Protocol-specified treatment modifications will be undertaken when significant toxic effects occur according to the Common Terminology Criteria for Adverse Events, version 4.0. Treatment discontinuation for severe toxicity or performance status deterioration/disease progression will be recorded. Patients discontinuing chemotherapy will not be considered for SBRT and will be included in the intention-to-treat analysis.

#### Restaging and indications for SBRT and surgical exploration

Patients completing chemotherapy will be re-staged with thin-slice contrast-enhanced tri-phasic computed tomography of the thorax and abdomen and re-evaluated at the Verona Pancreas Institute Oncologic meeting. Gadolinium-enhanced magnetic resonance will be considered in case of undetermined liver lesions (e.g. < 1 cm). Protocol prosecution will be indicated if surgical resection will be considered feasible. The minimum requirements for surgical eligibility will be partial response or stable disease according to the response evaluation criteria in solid tumors (RECIST) v1.1 [20] and a performance status of 0–1 (ECOG). Serum Ca 19.9 levels will be also considered in the decision process. An increase of Ca 19.9 values relative to the baseline will be considered a possible sign of progressive disease. Post-treatment values > 1000 U/L will be considered suspicious of micro-metastatic disease. In the instance of stable disease per RECIST criteria and increasing Ca 19.9 diagnostic laparoscopy will be considered.

SBRT will be considered only in surgical candidates, provided that:
There are no suspicious lymph nodes outside the planning target volume (PTV),There is no duodenal/gastric infiltration.

Patients not eligible for surgical exploration will not be considered for protocol prosecution, will be re-evaluated for possible second-line chemotherapy or maintenance chemoradiation, and will be included in the intention-to-treat analysis.

